The PATHWAY Group MCT multicentre, single-blind, randomised controlled trial aims to evaluate the effectiveness and cost-effectiveness of group-based metacognitive therapy for CR patients with elevated anxiety and/or depressive symptoms.^5^ Details of the main trial study protocol are available elsewhere.^5^ In brief, participants were recruited from patients with heart disease and referred for CR, in five UK National Health Service (NHS) Trusts. Trial participants had to meet CR eligibility criteria, score 8 or more on either the anxiety and/or depression subscale of the Hospital Anxiety and Depression Scale (HADS), be aged 18 years old or more and able to read, understand and complete questionnaires in English. Patients who gave informed consent to participate in the trial completed baseline assessments and were randomised via telephone link to Manchester Clinical Trials Unit. Participants were allocated to the intervention/comparator arms in a 1:1 ratio via a minimisation algorithm (incorporating a random component) to maximise balance between the two arms on gender, HADS score and hospital site. Participants randomised to the intervention arm received 6 weekly sessions of group-based metacognitive therapy delivered by either CR professionals or research nurses. The intervention and control groups were both offered in the usual CR programme within their Trust. The primary outcome is severity of anxiety and depressive symptoms at 4-month follow-up measured by the HADS total score.^13^ Secondary outcomes are severity of anxiety/depression at 12-month follow-up, health status, severity of post-traumatic stress symptoms, strength of metacognitive beliefs and service use at 4-month and 12-month follow-up. The PATHWAY Group MCT trial is part of a wider NIHR (National Institute for Health Research) programme grant for applied research, which began in August 2014 and with an end date of February 2021.

The aim of the economic evaluation component of the PATHWAY Group MCT trial is to estimate the cost-effectiveness of the addition of MCT intervention to CR for patients with elevated anxiety and/or depression symptoms, in a UK setting from a health and social care perspective. This will consist of a within trial analysis using patient-level data collected during baseline and follow-up study time points, and an economic model synthesising data from the trial and wider literature.

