### Within-trial analysis

The analysis will use individual patient-level service use and health benefit data from all participants recruited and allocated to a management arm in the PATHWAY Group MCT trial (n=332). The trial opened for recruitment in July 2015 and closed in January 2018, follow-up finished in February 2019. The economic analysis of trial data will begin in April 2020 and will complete by September 2020. The analysis will compare the addition of group-based MCT to usual CR versus usual CR alone (standard practice) for individuals with elevated symptoms of depression and/or anxiety. The study sample for the economic evaluation is all participants randomised to receive the group-based MCT plus usual CR, or usual CR only. In brief, participants were people eligible and offered (referred to) CR as per NHS trust protocol, with a HADS score of 8 or more on the anxiety and/or depression subscale. The intervention, usual care and participant inclusion and exclusion criteria are summarised and described in detail in the trial protocol.^5^ Usual CR (dependant on NHS site) includes varying degrees, psychological interventions to address distress such as relaxation, stress management and some cognitive challenging.

The time horizon of the within-trial primary cost-effectiveness analysis will be 12 months, to incorporate sufficient time for any impact of MCT on service use, subsequent costs and health benefit. This differs to the primary clinical effectiveness time horizon, which will be 4 months (note, a sensitivity analysis will look at cost-effectiveness at 4-month follow-up).^5^

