**Cardiac rehabilitation attendance (collected by the trial team**)	
Exercise cardiac rehabilitation	Number of attendances
Education cardiac rehabilitation	Number of attendances

*Examples include general practitioner.

†Examples include community-based mental healthcare and social support.

CD, compact disk; NHS, National Health Service.

**Table 2 T2:** Within-trial sensitivity analysis

Assumptions/variables	Changes	Rationale
Missing data are assumed to be missing at random	Complete case analysis Pattern mixture approach	The complete case analysis will use only the observed data and will provide insight to the result for the group of participants with complete follow-up and complete data (evaluable cohort). The pattern mixture approach will assess the impact of assuming that compliance and clinical outcomes are systematically worse in people with missing or with incomplete follow-up. It will be assumed that these differences will also lead to systematic worse health benefits and higher costs for participants with missing data^26 28^ The results of the complete case and pattern mixture analyses will be compared with the primary analysis based on multiple imputed data sets to give an indication of how robust the cost-effectiveness estimate is to assumptions about missing data.
Use of 1-month recall data	Assume that service use is equally distributed over the assessment period and that the 1-month data can be multiplied up to 4-month or 8-month follow-up. Add the 1-month cost estimates to the multiple imputation process, depending on the pattern of missing data and sufficient participants with both 1-month and 4-month or 8-month cost estimates.	The primary analysis treats the 1-month service use data as uninformative for participants who are missing data for the assessment period. These two sensitivity analyses explore the impact on the results of this approach.
Treatment received rather than intention-to-treat	The MCT group will only include those who attended at least one MCT session	The primary analysis will be an intention-to-treat approach. Recognising that not all patients assigned to the MCT intervention will attend, we will also run an analysis dividing the group using the recorded MCT attendance data.

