Single imputation will be used to impute missing baseline data. This simple approach is appropriate for baseline data, although in reality this is unlikely to have a significant impact as participants who have missing data at baseline are less likely to have follow-up data.^26 27^ Baseline variables are observed at entry to the trial and vary by the individual rather than random allocation to trial arms or values at follow-up. In contrast follow-up values for clinical and economic measures may be dependent on trial allocation and baseline. Accordingly, single imputation for baseline measures of cost, utility and clinical indicators ensures the estimated values are independent of treatment allocation and follow-up values. Single imputation is likely to be more efficient than multiple imputation. Multiple imputation (MI) will be used to impute missing follow-up data for costs and QALYs, which assumes that the data are missing at random (conditional on observed responses to clinical and economic measures and baseline covariates); MI of both costs and QALYs is recognised as an appropriate approach to deal with missing observation and missing follow-up data.^26^ Missing values will be imputed for each follow-up point. All missing follow-up cost and utility data will be assumed to be missing at random. To make best use of available data, we plan to impute costs by category (inpatient, outpatient and primary/community care) and utility by individual EQ-5D domain (mobility, self-care, usual activities, pain/discomfort and anxiety/depression). A balance is required between including all items and the stability of the imputation model if there is a high level of missing data. The stability of the model reduces as the number of variables with missing data increases. If feasible, all individual items in each cost category will be included in the imputation model. Total costs and QALYs (baseline to follow-up) will be generated using Stata passive estimation commands. The final imputation plan will be refined following a review of missing data (exploration of whether there are any patterns of missingness) and according to the patterns of service use and EQ-5D data. Two sensitivity analyses will explore whether the results vary by approach taken to missing data. The first will use complete case analysis. The second will use a pattern mixture approach that assumes compliance and clinical outcomes are systematically worse in people with missing or with incomplete follow-up.^26 28^ The specification of the analysis will be finalised after review of the complete and missing data patterns and discussion with clinical experts about plausible assumptions. If appropriate this analysis will identify the threshold values of compliance and clinical outcome that would lead to a change in conclusions about the relative cost-effectiveness of the within trial economic analysis.

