#### Primary analysis

Costs and health benefit for the primary and sensitivity analyses will be estimated from baseline to end of 12-month follow-up, to estimate the incremental cost-effectiveness of the addition of MCT intervention.

The primary measure of interest for the economic analysis is the incremental cost-effectiveness ratio (ICER). Rather than considering cost and health benefit separately, the ICER is a joint measure of both. It is calculated by dividing the difference in costs (net costs) by the difference in QALYs (net QALYs) between any two interventions. The ICER represents the additional cost of an intervention per additional QALY gained:

$$ICER=\frac{Cost_{MCTinterventionplususualcare}-Cost_{usualcare}}{QALYs_{MCTinterventionplususualcare}-QALYs_{usualcare}}$$

Note that if the intervention is cost saving and produces more QALYs when compared with usual care (ie, it falls in the South East quadrant of the cost-effectiveness plane), an ICER will not be presented as intervention is dominant in such a scenario. Likewise, if intervention is dominated (ICER lies in the North West quadrant of the cost-effectiveness plane) it will be described in this way rather than calculated and presented numerically.

Descriptive analysis and data manipulation will be conducted using SPSS V.25 and the main statistical analyses will be conducted in Stata V.15.

Regression analysis will be used to estimate the net costs and QALYs of MCT. Cost and QALY data may not be normally distributed. Graphical summaries and descriptive statistics will be used to assess the distribution of the pooled cost and QALY data and identify the appropriate regression models for the analysis (eg, generalised linear model with gamma, log distribution for costs). Key covariates will be included in the regression models to control for baseline factors that may influence costs or QALYs. The covariates for these analyses will be identified using the approach outlined for the multiple imputation described in the previous section.

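### The pattern-mixture analysis sets one direction of shift by missingness and none by arm; a common shift would largely cancel if missingness is similar between arms

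*Protocol article*

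**What the plan says.** The primary within-trial analysis uses multiple imputation for follow-up data, and the Missing data section states: "All missing follow-up cost and utility data will be assumed to be missing at random". Two sensitivity analyses address that assumption: a complete-case analysis and a pattern-mixture analysis.

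The pattern-mixture analysis is described in three places.

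- **Table 2** says it assesses the effect of supposing that "compliance and clinical outcomes are systematically worse in people with missing or with incomplete follow-up". It carries this over to the economic data as "systematic worse health benefits and higher costs for participants with missing data".
- **Missing data** says the approach "assumes compliance and clinical outcomes are systematically worse in people with missing or with incomplete follow-up". The specification is to be finalised after the missing-data patterns have been reviewed and clinical experts consulted. If this is judged appropriate, "this analysis will identify the threshold values of compliance and clinical outcome that would lead to a change in conclusions".
- **Discussion** repeats the clinical part of the assumption.

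None of the three mentions trial arm. Table 2 gives the purpose as comparison with the primary analysis, to show how far the cost-effectiveness result depends on missing-data assumptions. That result is built from contrasts between arms: the ICER is obtained by "dividing the difference in costs (net costs) by the difference in QALYs (net QALYs) between any two interventions".

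**The concern.** The scenario depends on whether a participant has missing data, while the decision depends on the difference between arms. If missing participants in both arms are moved by the same amount, the two arm means move together and most of the change drops out of net costs and net QALYs. The departures that could reverse a cost-effectiveness conclusion are those that differ by arm, for example if people lost from the MCT arm did worse than people lost from usual care. The scenario as stated does not commit to examining these. The Missing data section itself accepts that follow-up values may depend on allocation.

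The cost direction is also fixed. Non-responders who use fewer services than the imputation predicts are left out, without a reason given.

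This is the only planned analysis that models data missing not at random. Complete-case analysis imposes no such departure, and the Table 2 analyses of 1-month recall data use additional reported data rather than shifting missing values. The Discussion concedes that missing at random may not hold. If the one check is insensitive because of its form, an unchanged result could be read as robustness.

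**Working it through.** The article states no missingness rate, shift size or mean QALY, so there is no figure to reproduce. The check is an identity with illustrative numbers.

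**From the article**
- Sample: all participants "allocated to a management arm in the PATHWAY Group MCT trial (n=332"). Allocation is 1:1 (Introduction), so about 332 / 2 = 166 per arm.
- Quantity of interest: net costs and net QALYs (Primary analysis).
- Willingness to pay from £0 to £30 000 per QALY (Primary analysis); £20 000 is used here.

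**Assumed**
- Missing fractions pM (MCT) and pU (usual care) between 20% and 35%.
- Shift per missing participant: −0.05 QALY and +£500.

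**Identity.** With fraction p missing and missing values shifted by d from their imputed mean, the arm mean changes by p × d. Hence

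change in net estimate = pM × dM − pU × dU.

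With a common shift, dM = dU = d, this is d × (pM − pU). It is zero when pM = pU, whatever the size of d.

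**Net benefit.** One shifted participant contributes 20 000 × (−0.05) − 500 = −£1500. Therefore:

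| pM v pU | Common shift | MCT only | Usual care only |
|---|---|---|---|
| 20% v 20% | £0 | −£300 | +£300 |
| 30% v 30% | £0 | −£450 | +£450 |
| 25% v 20% | −£75 | −£375 | +£300 |
| 30% v 20% | −£150 | −£450 | +£300 |
| 35% v 20% | −£225 | −£525 | +£300 |

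For 30% v 20%, the common shift gives net QALYs 0.10 × (−0.05) = −0.005 and net cost 0.10 × 500 = +£50, so net benefit changes by −100 − 50 = −£150. Doubling both shifts doubles every entry.

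The common shift has (pM − pU) / pM of the MCT-only effect: 0 at equal missingness, 1/5 at 25% v 20%, 1/3 at 30% v 20% and 3/7 at 35% v 20%.

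**QALY shift alone.** Assume a mean QALY of 0.70, made 10% worse, so 0.07. At 20% in each arm, a common shift gives £0, and MCT only gives 0.20 × 0.07 × 20 000 = £280 lower. At 25% v 20% the figures are 0.05 × 0.07 × 20 000 = £70 lower and 0.25 × 0.07 × 20 000 = £350 lower.

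**Threshold search.** Suppose the primary net benefit were £300 in favour of MCT (an assumption). At 25% v 20%, an MCT-only shift reaches zero at 300 / 0.25 = £1200 per missing participant. A common shift needs 300 / 0.05 = £6000. At equal missingness no common shift reaches zero.

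**Cost direction.** With −0.05 QALY and −£500, a shifted participant contributes −1000 + 500 = −£500. MCT only at 20% is then −£100 rather than −£300, so the sign of the cost shift matters once shifts can differ by arm.

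**Multiplicative cost shifts.** If missing costs are multiplied by 1 + k, net cost changes by k × (pM × mM − pU × mU), where mM and mU are the imputed mean costs among the missing. At equal p this leaves k × p × (mM − mU), so cancellation is approximate rather than exact.

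**The case against.** The strongest reply is that the article does not describe a common shift at all. It gives a direction for people with missing data and is silent on arm, which is compatible with different magnitudes in each arm. The Missing data section leaves the final specification open and allows a threshold search. In a journal article, values by arm and tipping-point grids can properly be left to a fuller plan.

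Much of this stands. A reader might infer that missing participants are shifted identically in both arms, and that the analysis therefore cannot test robustness. The documents support neither statement. Equal shifts are the natural reading, but they are not written down. Cancellation is incomplete if missingness differs by arm, and the rates are not given. It is only approximate for multiplicative cost shifts. Any part of the compliance assumption that concerns MCT attendance exists in one arm only and would not cancel.

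Three things remain. The article does fix something: conditioning on missingness, and one direction for both health and cost. What is deferred sits beneath that stated assumption, and the threshold search is conditional and framed in terms of compliance and clinical outcome without an arm dimension. And MCT attendance is recorded by the trial team (Table 1), so worse compliance does not clearly supply an arm-specific shift for the missing questionnaire costs and EQ-5D. Choosing a single cost direction is defensible as one scenario, but it is narrow when it is the only one named.

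**Conclusion.** The point holds in conditional form. If a common shift is applied and missingness is similar between arms, the pattern-mixture analysis is a weak test of departures from missing at random and could suggest robustness because of how it is built. In the illustration the loss of sensitivity is complete at equal missingness (£0 against £300 in either direction at 20%), and two thirds at 30% v 20% (−£150 against −£450 for MCT only). These amounts rest on assumed missing fractions, shifts and, in one example, mean QALY; the identity itself does not depend on them. This is an inexpensive improvement to a stated method. It does not show that the analysis will fail, since the deferred specification could still adopt shifts by arm.

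**What to change.** In Table 2 and the Missing data section, state that the QALY and cost shifts for missing participants will be varied separately by arm: MCT only, usual care only, and both. Let cost shifts run in both directions. Report net benefit over that grid, and the tipping point at which the conclusion changes, as a planned output rather than a conditional one. Fix this structure before results by arm are seen; the sizes of the shifts can still be settled after the review of missing-data patterns and the discussion with clinical experts. Reporting the missing fractions by arm alongside would let readers judge how much of a common shift cancels.

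The cost is a change of wording, a loop over the existing imputed data sets, and more output to report. No new data are needed.

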Time horizon	4 months	The final trial time follow-up is 12 months. A secondary analysis will consider the 4-month follow-up (the primary follow-up of the trial), to assess the impact of different follow-up periods on cost-effectiveness results.

Adherence to CR has been defined by the study team as the attendance to four or more sessions to each component of usual CR (exercise sessions and educational talks).

CR, cardiac rehabilitation; MCT, metacognitive therapy; QALY, quality-adjusted life-year.

Note that from the reported service use, psychological treatment outside of cardiac rehabilitation and MCT will also be costed. MCT attendance data collected during the trial by the research team will be used to estimate a per participant cost for the MCT intervention. In the primary analysis, this will include staff costs and the cost of materials. The average group size from the trial will be used to calculate a cost per session per participant, which will be multiplied by the number of sessions attended by each participant. Staff time to deliver MCT and attendances at cardiac rehabilitation will be collected by the research team.

The unit costs of NHS and social care services will be derived from national average unit cost data. These unit costs are published annually in the NHS reference costs database, and in the Unit Costs of Health and Social Care document published by the Personal Social Services Research Unit, University of Kent. The price year for all costs will reflect the most recent unit costs at the time of analysis. The total direct costs of service use for each trial arm (including MCT and cardiac rehabilitation) will be estimated by summing the costs of each resource by the reported use to provide health and social care.

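### The treatment-received sensitivity analysis compares MCT attenders with everyone in usual CR and so is open to selection bias; a complier-average analysis would keep the randomised comparison

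*Protocol article*

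**What the plan says.** Table 2 of the protocol article, under Resource use and costs, lists a treatment-received analysis among the within-trial sensitivity analyses. Its rule is that "The MCT group will only include those who attended at least one MCT session". The row confirms that the primary analysis is by intention to treat. It gives incomplete uptake of MCT as the reason for adding this second analysis, and describes the method in these words: "we will also run an analysis dividing the group using the recorded MCT attendance data". The row sets no condition on the usual-CR arm and carries no caution about interpretation.

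Other parts of the article bear on this:

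- Introduction: "Participants were allocated to the intervention/comparator arms in a 1:1 ratio via a minimisation algorithm", with a random component. The Within-trial analysis section gives the number randomised as 332.
- Primary analysis (within-trial): baseline covariates enter the cost and QALY regressions.
- Resource use and costs: MCT is costed per session and participant, "which will be multiplied by the number of sessions attended by each participant". Table 1 also lists a paper manual and a CD as MCT resources.
- Handling uncertainty: the sensitivity analyses test how study design affects the ICER and the acceptability results. The Discussion says they test the results and conclusions of the primary analysis.

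**The concern.** Attendance is decided after allocation and may depend on health, motivation or circumstances. It is known only for people offered MCT, so no equivalent group can be picked out of the usual-CR arm. The rule therefore removes would-be non-attenders from one side of the comparison and leaves them in the other. The difference that results mixes the effect of MCT with the difference between people who attend and people who do not.

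The primary result is not at stake. What is at stake is how this row is used. The article presents its sensitivity analyses as tests of the primary conclusions. The subgroup row of Table 2 is marked as highly exploratory, but this row has no such warning. A reader who sees the ICER move under the attenders-only rule could not tell whether that reflects treatment, selection or chance.

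**Working it through.** The article gives no attendance rate, outcome SD, expected effect or prognostic gap, so there is no stated figure to reproduce. The check is algebraic, with assumed inputs to show scale.

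**Notation.** Let p be the proportion who attend at least one session when offered MCT. Let g be the mean under usual CR for would-be attenders minus that for would-be non-attenders, after any covariate adjustment. Let τ be the effect of MCT in attenders. Assume that an offer without attendance changes nothing and that nobody in usual CR receives MCT.

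- Usual-CR mean, relative to would-be attenders: −(1 − p)g
- Attenders in the MCT arm: τ
- Attenders-only comparison: τ + (1 − p)g, so the bias is (1 − p)g
- Intention-to-treat difference: pτ
- Complier-average estimate: pτ / p = τ

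**Scale of the QALY bias (assumed: non-attendance 10% to 30%, g 0.05 to 0.10 QALY).**

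- Low end: 0.10 × 0.05 = 0.005 QALY; × £20 000 = £100
- High end: 0.30 × 0.10 = 0.03 QALY; × £20 000 = £600

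**Worked illustration with costs (all inputs assumed).** MCT has no QALY effect and costs £200 per attender. Under usual CR, non-attenders have 0.05 fewer QALYs and £500 higher costs than attenders. At £20 000 per QALY the true net benefit in attenders is 0 − £200 = −£200.

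| p | Net QALY, (1 − p) × 0.05 | Net cost, £200 − (1 − p) × £500 | Attenders-only net benefit | Net benefit if both gaps are reversed |
|---|---|---|---|---|
| 0.6 | 0.020 | £0 | +£400 | −£800 |
| 0.7 | 0.015 | £50 | +£250 | −£650 |
| 0.8 | 0.010 | £100 | +£100 | −£500 |
| 0.9 | 0.005 | £150 | −£50 | −£350 |

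The last column changes the sign of both gaps. At p = 0.8, for example, net QALY is −0.010 and net cost is £300, so net benefit is −£200 − £300 = −£500. The bias has the same size in either direction. With no gap the attenders-only and complier-average estimates agree, so the whole discrepancy is selection.

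**Simulation of the first case** (166 per arm assumed from 1:1 allocation, SD 0.25 QALY and £3000 assumed, 4000 runs). The share of trials with positive net benefit at p = 0.6, 0.7, 0.8 and 0.9 was:

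- attenders-only rule: 0.69, 0.63, 0.56 and 0.47
- intention-to-treat and complier-average alike: 0.41, 0.41, 0.40 and 0.39

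**What the complier-average analysis does to the ICER.** In the unadjusted linear case it is (ΔC / p) / (ΔQ / p) = ΔC / ΔQ, which is the intention-to-treat ICER. Net cost, net QALYs and net benefit are rescaled by 1/p.

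**Precision.** With equal arms and equal variances, the standard error of the complier-average estimate divided by that of the attenders-only difference is about (√2 / p) / √(1/p + 1). At p = 0.8 this is 1.768 / 1.5 = 1.18; at p = 0.6 it is 2.357 / 1.633 = 1.44.

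**The case against.** The case for leaving the row alone has several parts.

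- **It is only a sensitivity analysis.** The primary analysis is intention-to-treat, and the row claims no causal effect among attenders. This stands, and it limits the weight of the point. It does not justify using a comparison open to selection bias as a test of the primary conclusions.
- **Covariates are adjusted for.** This also stands in part. The gap that matters is the one left after adjustment, which may be smaller than a raw gap. Baseline variables cannot be relied on to capture motivation, or changes in health after randomisation.
- **The remedy adds little to the ICER.** This is correct in the unadjusted linear case and should be disclosed. The gain is in net cost, net QALYs and net benefit among attenders.
- **The exclusion restriction is not guaranteed.** This is fair. Per-session costing makes it plausible for session costs, but the article does not say whether non-attenders received the manual or CD.

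A reader might also infer that the bias favours MCT, from the pattern-mixture row's rationale of "assuming that compliance and clinical outcomes are systematically worse in people with missing or with incomplete follow-up". That text is a stress test about missing follow-up. It does not say that people who skip MCT would have done worse under usual CR. More distressed patients might attend more, or recovering patients less, and the article does not settle it.

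The phrase about dividing the group might suggest that non-attenders are moved into the comparator. The article does not say so, and may leave that detail to the full plan.

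**Conclusion.** The point holds as a matter of design. As written, the rule compares participants selected on a post-randomisation variable with an unselected arm, and baseline adjustment may lessen the bias without reliably removing it. The intention-to-treat result is not affected.

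Direction and size in this trial are unknown. The range of 0.005 to 0.03 QALY (£100 to £600 at £20 000 per QALY) rests wholly on the assumed attendance and gap. A reader might infer that a bias of this order rivals the entire benefit that MCT could show in 12 months. The article gives no expected benefit, so that comparison cannot be made.

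The change is worth making because it answers the same question with data already collected, and because the row is presented as evidence on robustness.

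**What to change.** Replace the row in Table 2 with a complier-average causal effect analysis:

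- Keep all 332 participants in the arm to which they were randomised.
- Use allocation as the instrument for attending at least one MCT session.
- Estimate net cost and net QALYs jointly on the multiply imputed data, with the baseline covariates. Two-stage least squares or a bivariate instrumental-variable model would serve.
- Report net cost, net QALYs and net benefit among compliers.
- State the exclusion restriction, including whether non-attenders received the manual or CD, and the assumption that nobody in the usual-CR arm had access to MCT.
- Note that in the unadjusted linear case the ICER equals the intention-to-treat ICER.

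If the attenders-only comparison is also shown, label it descriptive, say how non-attenders are handled, and do not present it as a robustness check of the primary result.

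The cost is a reworded table row and a standard analysis in Stata, which is already the planned software. Attendance is already recorded, so no new data are needed. Intervals will be wider than for the attenders-only subset, and the added assumptions have to be defended in the report.
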